## Abstract

**Background:**

Invasive pulmonary aspergillosis (IPA) has been increasingly reported in patients with underlying respiratory diseases (URD). Early diagnosis of IPA is crucial for mortality reduction and improved prognosis, yet remains difficult. Existing diagnostic tools for IPA largely rely on the detection of biomarkers based on serum or bronchoalveolar lavage fluid (BALF), both of which have their limitations. The use of sputum sample is non-invasive, and *Aspergillus* detection is feasible; however, the usefulness of sputum biomarkers for the diagnosis of IPA, especially in patients with URD, has not been systematically studied.

**Methods:**

This is a prospective diagnostic trial. At least 118 participants will be recruited from respiratory wards and intensive care units. IPA is defined according to the EORTC/MSG criteria modified for patients with URD. Induced sputum and blood will be collected, and BALF will be obtained by bronchoscopy. Sputum biomarkers, including galactomannan, *Aspergillus* DNA, triacetylfusarinine and bis(methylthio)gliotoxin will be determined, and the presence of a JF5 antigen will be examined with a lateral fluid device. The sensitivity, specificity, negative predictive value, positive predictive value and diagnostic odds ratio will be computed for different biomarkers and compared using the McNemar χ^2^ test. Receiver operating characteristic analyses will be performed, and the cut-off values will be established. Participants will receive follow-up evaluations at 3 months and 6 months after recruitment. The difference in hospital stay and survival will be analysed, and the relationships between the levels of biomarkers and hospital stay and survival will be analysed via regression models.

**Discussion:**

We have developed and verified the feasibility of *Aspergillus*-related biomarker assays for sputum. The study findings will contribute to a novel look at the diagnostic performance of sputum biomarkers in IPA and provide important insight into the improvement of the early diagnosis of IPA, particularly in patients with URD.

**Trial registration:**

This study has been registered with the Chinese Clinical Trial Registry (ChiCTR-DPD-16009070) on 24th of August 2016.

## Background

Invasive pulmonary aspergillosis (IPA) is a fungal infection that occurs primarily in patients with severe immunodeficiency [1]. In recent years, IPA has been increasingly recognized in patients without haematologic malignancy or organ transplantation [2–9], especially in those with underlying respiratory diseases (URD) [2–5, 10–12]. Remarkably, the mortality rate among non-neutropenic patients was significantly higher than that in neutropenic patients [12], such that a mortality rate of greater than 90% in patients with chronic obstructive pulmonary disease was reported [13].

Although a favourable clinical outcome of patients with IPA is largely influenced by the initiation of effective antifungal treatment [14], the early diagnosis of IPA is still notoriously difficult, and few diagnostic tools are available [15]. The “gold standard” to confirm the diagnosis is the histopathological examination of lung tissue obtained by thoracoscopic or open-lung biopsy [16]. Considering its limitation in terms of feasibility and sensitivity in clinical practice, the European Organization for Research and Treatment of Cancer/Mycoses Study Group (EORTC/MSG) proposed diagnostic criteria for IPA that integrate host factors, clinical evidence and mycological findings [17]. However, the diagnosis of IPA in patients with URD remains challenging. The host factors defined by the EORTC/MSG framework do not necessarily apply to patients in the respiratory wards or intensive care units [2], and the official group recognized this as “an omission” [17].

A variety of sample types and biomarkers have been explored and validated in the journey to seek mycological evidence for the diagnosis of IPA, and different methodologies and matching signatures have been investigated (Fig. 1). Direct mycological proof by culture is rarely feasible due to the low sensitivity and long turnaround time [18, 19]. Therefore, indirect tests that detect *Aspergillus*-related biomarkers, e.g., galactomannan (GM), in body fluids were developed, showed improved diagnostic performance and were included in the EORTC/MSG framework [17]. Serum biomarkers, in particular, *Aspergillus* DNA (*A*-DNA) and GM, have been intensively studied in haematological patients in the past two decades which exhibited good performance [20, 21]. However, these tests had lower sensitivity when applied in non-haematological patients [22, 23], probably because non-neutropenic patients tend to develop airway invasive aspergillosis instead of angioinvasive aspergillosis [24, 25]. This further indicates that biomarker detection based on organ specific samples may be associated with better diagnostic performance for IPA in non-neutropenic patients. Indeed, biomarker detection using bronchoalveolar lavage fluid (BALF) has been found to be associated with a higher diagnostic accuracy for IPA compared to serum in these patients [6–8, 26]. However, bronchoscopy is an invasive procedure and is not feasible for all patients in clinical practice. In contrast, induced sputum sampling is non-invasive, convenient and low cost and, if successful, often precludes the need for bronchoscopy. Sputum is expectorated from local sites of infection and can be used for microbiologic examinations, therefore, it has the potential to be used for biomarker determination in IPA.

**Fig. 1 Fig1:**
[figure not shown]
Current biomarkers for the diagnosis of IPA using different sample types. Abbreviations: *A*-DNA = aspergillus DNA; bmGT = bis(methylthio)gliotoxin; GM = galactomannan; PCR = polymerase chain reaction; TAFC = triacetylfusarinine

We searched the literature using the terms “sputum”, “sputa”, “bronchial secretion”, “bronchial aspirate”, “respiratory sample” and “aspergillosis”, “*Aspergillus*” in Medline, EMBASE and PubMed databases up to the 20th of May 2017. Seven studies that assessed the GM assay with sputum samples were identified (Table 1), of which only the study by Kimura et al. [27] tested the efficacy of sputum GM for the diagnosis of IPA in haematological patients in a well-designed manner. The results of this study identified a sensitivity of 100% and a specificity of 62.2% for sputum GM at the cut-off value of 1.2 optical density index (ODI). However, the small sample size impeded the external validity of the study and the validation of an optimal cut-off value. Some studies have assessed *A*-DNA in sputum via the polymerase chain reaction (PCR) assay; however, these studies exclusively aimed at identifying the existence of *Aspergillus* in sputum rather than assessing the diagnostic performance for IPA [28–31]. Fraile et al. [32] and Chanzá et al. [33] intended to evaluate the sputum PCR assay for the diagnosis of IPA; however, diagnostic criteria according to the EORTC/MSG framework were not applied. Our study will use real-time PCR (RT-PCR) to detect sputum *A*-DNA for IPA in patients with URD diagnosed by the EORTC/MSG criteria.

**Table 1 Tab1:** Studies assessing sputum GM assay for various *Aspergillus* events

Author	Year	*Aspergillus* events	Underlying diseases	Sputum type
Kimura [27]	2009	IPA	HD	spontaneous/induced
Fraile [32]	2012	IPA^a^	not classified^b^	not reported
Delfino [34]	2012	AC	cystic fibrosis	not reported
Baxter [29]	2013	AC	cystic fibrosis	spontaneous
Baxter [28]	2013	ABPA	cystic fibrosis	spontaneous
Chanzá [33]	2014	IPA^a^	HD and NHD	not reported
Dhillon [35]	2016	ABPA	cystic fibrosis	not reported

*Abbreviations*, *ABPA* allergic bronchopulmonary aspergillosis, *AC Aspergillus* colonization, *HD* haematological disease, *IPA* invasive pulmonary aspergillosis, *NHD* non-haematological disease

^a^EORTC/MSG diagnostic criteria were not used.

^b^Patients recruited from Infectious, Pneumology, Oncology Services and Critical Care Unit, without specific underlying diseases classified.

Several other biomarkers that either target *Aspergillus* antigens or *Aspergillus*-related metabolites have been proposed for the diagnosis of IPA in recent years (Fig. 1) by a systematic literature review. Thornton et al. [36] developed a lateral flow device (LFD) that could be used at bedside to detect the JF5 antigen, an *Aspergillus* glycoprotein secreted during active fungal growth, which showed better diagnostic performance than GM in serum and BALF. Triacetylfusarinine (TAFC) and bis(methylthio)gliotoxin (bmGT) are toxic metabolites of *Aspergillus* and have been assayed by liquid chromatography tandem mass spectrometry in serum of haematology patients [37] or neutropenic patients, respectively. The above *Aspergillus*-related signatures present appropriate diagnostic accuracy for the diagnosis of IPA, yet have not been assessed in sputum samples or in patients with URD.

A study exploring the usefulness and diagnostic performance of sputum biomarkers for IPA in patients with URD is absent. Considering the incidence and high mortality of these patients and the great potential of using a sputum sample for *Aspergillus* detection, we will conduct this study to examine a broad spectrum of approaches and biomarkers related to *Aspergillus* detection using sputum samples from patients with URD to investigate the diagnostic performance of these sputum signatures for IPA in this study population. This study may help provide novel and useful diagnostic modalities, stepping over the existing obstacles to an early diagnosis of IPA in clinical practice.

## Methods/design

### Study design

This is a prospective diagnostic trial. The study protocol has been registered with the Chinese Clinical Trial Registry (ChiCTR-DPD-16009070). Participants will be enrolled from respiratory wards and intensive care units in the West China Hospital, Sichuan University of China. Inclusion criteria are patients (1) with URD including chronic pulmonary diseases (COPD, asthma, lung cancer, bronchiectasis, interstitial lung diseases, and cystic fibrosis) and acute pulmonary diseases (bacterial pneumonia, viral pneumonia, and acute bronchitis); (2) willing to provide informed consent; and (3) able to tolerate sputum induction. Exclusion criteria are patients (1) with underlying haematological malignancies; or (2) that are previous receipts of solid organ transplant; or (3) that are unable to produce sputum.

### Diagnostic criteria

The diagnostic criteria of IPA are based on the 2008 EORTC/MSG framework [17]. Host factors, clinical criteria and mycological criteria to establish the diagnosis of IPA in this study population are listed in Table 2. In accordance with the study by Prattes et al. [11], URD is added as one of the host factors. We propose to make this modification due to several reasons. Host factors of the diagnostic criteria in previous guidelines were originally defined for haematological patients but have not been validated in non-neutropenic patients. Additionally, those typical host factors promoted by EORTC/MSG are frequently absent in non-haematological patients [2, 23]. Patients will be classified into proven, probable, possible and no IPA groups according to the revised 2008 EORTC/MSG criteria [17] (Table 3).

**Table 2 Tab2:** The diagnostic framework for IPA in patients with URD

Host factors	Recent history of neutropenia (< 0.5 × 10^9^ neutrophils/L for > 10 days) temporally related to the onset of infection Prolonged use of corticosteroids at a mean minimum dose of 0.3 mg/kg/day of prednisone equivalent for > 3 weeks Treatment with immunosuppressants during the past 90 days Inherited severe immunodeficiency Underlying respiratory diseases including chronic pulmonary diseases (COPD, asthma, lung cancer, bronchiectasis, interstitial lung diseases, and cystic fibrosis) and acute pulmonary diseases (bacterial pneumonia, viral pneumonia, and acute bronchitis)
Clinical criteria	The presence of 1 of the following 3 signs on chest computed tomography: Dense, well circumscribed lesion(s) with or without a halo sign Air-crescent sign Cavity on chest computed tomography
Mycological criteria	Cytologic or microscopic evidence of *Aspergillus* elements or recovery of *Aspergillus* in sputum or BALF Positive GM test in serum or BALF

**Table 3 Tab3:** IPA classification according to revised 2008 EORTC/MSG criteria

Proven IPA	Histopathological or cytopathological examination of lung tissue showing *Aspergillus* hyphae from needle aspiration or biopsy specimen with evidence of associated tissue damage, OR positive culture result for *Aspergillus* from a sample obtained by sterile procedure from the lung.
Probable IPA	Host factors, AND clinical criteria, AND mycological criteria
Possible IPA	Host factors AND clinical criteria
No IPA	Other cases excluded from proven, probable and possible IPA groups

### Participants screening and recruitment

The study flowchart is shown in Fig. 2. Patients with respiratory diseases admitted into the hospital will be screened for inclusion and exclusion criteria for recruitment. The recruited patients will be subsequently assessed according to the clinical criteria shown in Table 2, namely newly-developed abnormalities in CT scan associated with IPA, for the classification of no IPA or suspected IPA groups. Patients without clinical criteria will be identified as no IPA. For patients with typical clinical criteria, those presenting histopathological or cytopathological evidence of *Aspergillus* hyphae from needle aspiration or biopsy specimen, or positive culture result for *Aspergillus* from a sample obtained by sterile procedure from the lung will be identified as proven IPA. If lung biopsy is not performed or negative result is generated, mycological examinations will be performed including sputum/BALF culture or serum/BALF GM tests to further classify patients as probable or possible IPA. Sample collection and testing will be required to be performed prior to antifungal treatment.

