### Statistical analysis

The data will be analysed with SPSS 22.0 software (IBM Corp, Armonk, NY, USA). Two analyses will be performed based on the IPA classification, one in which patients with possible IPA will be excluded in the calculation and a second analysis in which patients with possible IPA will be classified as not having IPA. Therefore, the comparisons and analyses will be (1) proven/probable IPA versus no IPA, and (2) proven/probable IPA versus possible/no IPA [43]. The sensitivity, specificity, negative predictive value (NPV), positive predictive value (PPV), and diagnostic odds ratio, including 95% confidence intervals, will be calculated for different biomarkers. ROC analysis will be performed and AUC (including 95% CI) and cut-off values will be established from the ROC curves for GM, RT-PCR, TAFC and bmGT. The McNemar χ^2^ test will be used to compare sensitivity, specificity, NPV, and PPV between different assays. The difference in hospital stay and the survival between possible or no IPA versus proven or probable IPA will be analysed with chi-square tests, and the relationships between the levels of biomarkers and the hospital stay and survival will be analysed via regression models. *P* < 0.05 will be defined as statistically significant.

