## Discussion

The clinical and radiological features of IPA are atypical, leading to the difficulty in an early diagnosis and treatment of the disease. There are still uncertainties and controversies associated with the diagnosis of IPA in clinical practice. Intensive efforts have been made to improve the diagnosis in “high-risk” individuals such as haematological and immunocompromised patients. Consequently, a series of approaches have been developed attempting to access a precise diagnosis.

Biomarker development has opened new possibilities in the diagnosis of a great number of disorders including IPA. Biomarkers related to IPA have been isolated and investigated largely in serum or BALF sample, yet few study has addressed the possibility of sputum biomarkers in the diagnosis of IPA. Each sample type has its advantages as well as disadvantages (Table 5). Biomarker detection using serum is convenient, inexpensive and time-saving, presenting high specificity [20], however the sensitivity was reported to be low in non-haematological patients [6, 23, 44, 45]. In comparison, BALF assays exhibit higher sensitivity as well as specificity in both neutropenic [46] and non-neutropenic patients [7, 9], probably because BALF is retrieved from local airways. However, the bronchoscopy is an invasive and costly procedure, and it might not be accessible to severe patients or those with contraindications.

**Table 5 Tab5:** Pros and cons of serum, BALF and sputum samples for IPA diagnosis in non-haematological patients

Samples	Pros	Cons
Serum	□Convenient, cheap and fast □High specificity	□Low sensitivity
BALF	□Local-infection related □High sensitivity and specificity	□Invasive, having contraindications □Expensive
Sputum	□Convenient, cheap and fast □Local-infection related □Non-invasive	□Affected by colonization and contamination

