Potential diagnostic biomarkers for IPA have been intensively studied, given the problem of an early diagnosis. We have reviewed the literature systematically to identify potential biomarkers that can be detected in a sputum sample. Galactomannan (GM) is a cell wall polysaccharide that is released by *Aspergillus* during fungal growth. The method of GM detection has been commercialized and widely used in the clinic with serum and BALF samples [19]. The serum GM assay exhibits low sensitivity (23.1–42%) for the diagnosis of IPA in non-haematological patients [6, 23], whereas BALF GM shows higher sensitivity and specificity [6–9]. The GM assay for sputum samples has been established in several studies (Table 1). Whether a GM assay based on lower airway derived sputum can be used as a non-invasive tool for the diagnosis of IPA deserves investigation. The measurement of GM in sputum might provide a more sensitive and non-invasive diagnostic approach for IPA.

GM detection can be affected by non-*Aspergillus* fungi and food that contains GM and beta-lactam antibiotics, which can produce false-positive values [49–51]. Several other biomarkers have been shown to play a role in the diagnosis of IPA and may be potential candidates for future clinical use. A rapid detection with LFD is an immunochromatographic assay that uses a monoclonal antibody called JF5 that targets an extracellular glycoprotein secreted during active fungal growth [36]. The test can be performed bedside and accomplished within 15 mins and, therefore, can be used as an early indicator for *Aspergillus* infection. The device is highly specific to antigens from *Aspergillus* but does not react with antigens from a large number of clinically important fungi, especially *Candida species* [36]. Pan et al. [52] conducted a meta-analysis to investigate its diagnostic accuracy for invasive aspergillosis, and showed that the LFD assay using BALF had higher sensitivity (86%) and specificity (93%) than serum (68% sensitivity and 87% specificity). Importantly, the BALF LFD assay also exhibited satisfying diagnostic performance for IPA (77% sensitivity and 92% specificity) in patients with URD [11]. Sputum supernatant has a similar matrix as BALF after processing procedures; hence, the use of the sputum LFD assay may provide a bedside and time-saving diagnostic tool for IPA.

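### Whether a suspected patient is labelled probable or possible IPA depends partly on whether BALF was obtained, and analysis 2 counts every possible patient as non-IPA

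*Protocol article*

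**What the plan says.** **Classification.** Under Participants screening and recruitment, a patient with a qualifying CT sign and no proof from tissue or a sterile sample is sorted as follows: "mycological examinations will be performed including sputum/BALF culture or serum/BALF GM tests to further classify patients as probable or possible IPA". Table 2 (Diagnostic criteria) accepts either specimen for each test: "recovery of *Aspergillus* in sputum or BALF" for culture, and "Positive GM test in serum or BALF" for galactomannan (GM). Table 3 defines probable IPA as "Host factors, AND clinical criteria, AND mycological criteria". Possible IPA needs the first two of these only. No minimum set of mycological tests is stated. A patient without CT criteria is no IPA, whatever the mycology.

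**Analyses.** Under Statistical analysis, analysis 1 leaves possible IPA out. In analysis 2, "patients with possible IPA will be classified as not having IPA".

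**Who has BALF.** The Abstract says without qualification that BALF will be obtained, and the Discussion says that serum and BALF will be collected and compared. Study design, however, requires tolerance of sputum induction and says nothing about bronchoscopy, and it enrols from intensive care units as well as wards. The Background says "bronchoscopy is an invasive procedure and is not feasible for all patients in clinical practice", and the Discussion says of bronchoscopy that "it might not be accessible to severe patients or those with contraindications".

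**The concern.** Two patients with the same disease can receive different labels because one had BALF and the other did not. Without BALF, the label rests on sputum culture or microscopy and on serum GM. The Discussion says: "The serum GM assay exhibits low sensitivity (23.1–42%) for the diagnosis of IPA in non-haematological patients". It also says that BALF GM is more sensitive, without giving a figure. The Background calls culture insensitive in general terms. True IPA without BALF is therefore more likely to stay at possible.

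The possible category then mixes patients whose BALF was negative with patients whose BALF was never examined. Analysis 2 treats both as disease-free. A correct positive sputum result in an unverified case is scored as a false positive, so apparent specificity, PPV and AUC fall. If BALF is missing mainly in sicker patients, as the Discussion suggests it might be, the misclassification is also not random. The two analyses are meant to show how much the possible group matters, but neither separates unverified from test-negative patients.

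**Working it through.** **1. The plan's own figure.** With the stated formulas, a = 1.414 × Φ⁻¹(0.795) = 1.165, V = 0.0099 × exp(−a²/2) × (6a² + 16) = 0.1213, and n = 1.96² × 0.1213 / 0.09² = 57.5, so 58 per group against the stated 59. The difference is immaterial and not at issue. The 59 is used below as a group size.

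**2. Inputs.**
- From the protocol: serum GM sensitivity 0.231–0.42.
- Assumed, because the protocol gives no figure: sputum culture sensitivity 0.30–0.50, BALF GM sensitivity 0.70–0.90, and tests independent given disease.

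**3. True IPA left at possible.**
- Without BALF, (1 − serum GM)(1 − culture): 0.769 × 0.70 = 0.54 down to 0.58 × 0.50 = 0.29.
- With BALF GM added, multiply by (1 − BALF GM): 0.54 × 0.30 = 0.16 down to 0.29 × 0.10 = 0.03.

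So 29–54% without BALF, against 3–16% with it. With other assumptions (culture 0.20–0.40, BALF GM 0.60–0.90), the probability of being labelled probable is 0.39–0.65 without BALF and 0.75–0.97 with it. The direction is the same.

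**4. Analysis 2 specificity, all missed IPA.** Assume 59 no IPA and 30 possible, of whom 15 truly have IPA, and a marker with true sensitivity 0.85 and specificity 0.80.
- Apparent specificity = [(59 + 15) × 0.80 + 15 × 0.15] / 89 = 61.45 / 89 = 0.69, a fall of 0.11.
- With 20–40 possible patients, 30–70% of them truly IPA, it runs from (73 × 0.80 + 6 × 0.15) / 79 = 0.75 to (71 × 0.80 + 28 × 0.15) / 99 = 0.62.

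**5. The part due to missing BALF.** Some IPA is missed even when everyone has BALF. With 59 labelled cases, step 4 has 59 + 15 = 74 true IPA. If all had BALF, 3–16% would be missed:
- 2.1 missed: (74 × 0.80 + 2.1 × 0.15) / 76.1 = 0.78.
- 11.9 missed: (74 × 0.80 + 11.9 × 0.15) / 85.9 = 0.71.

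Missing BALF therefore accounts for 0.78 − 0.69 = 0.09 down to 0.71 − 0.69 = 0.02 of the 0.11. Step 4 has 15/74 = 20% missed. That implies a share without BALF of (0.203 − 0.029) / (0.290 − 0.029) = 67% at the high-sensitivity end, and (0.203 − 0.161) / (0.538 − 0.161) = 11% at the low end.

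**6. Varying the share with bronchoscopy.** Serum GM 0.33 lies within the protocol's range, and marker specificity 0.622 is the value the Background reports for sputum GM. Assumed: culture 0.30, BALF GM 0.80, marker sensitivity 0.80, 100 suspected true IPA, 40 suspected non-IPA and 100 no IPA. The correlated columns assume marker sensitivity 0.95 in sputum-culture-positive cases.

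| Share with BALF | Analysis 2 specificity, marker independent of culture | Analysis 2 specificity, correlated | Sensitivity in both analyses, correlated |
|---|---|---|---|
| 100% | 0.596 | 0.600 | 0.807 |
| 50% | 0.551 | 0.562 | 0.825 |
| 0% | 0.516 | 0.532 | 0.857 |

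Under independence, sensitivity stays at 0.80 in both analyses. Analysis 1 specificity stays at 0.622 throughout, because its controls are set by CT alone.

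**The case against.** - **Incomplete BALF is inferred.** The protocol never says that only some suspected patients have bronchoscopy. The Abstract and Discussion point the other way, the remarks on access concern clinical practice in general, and the flowchart that might settle it is not in the text reviewed. This stands. A reader might infer that differential verification is part of the design; the text only leaves it open. The passages still conflict, and the classification rule would accommodate missing BALF without showing it.
- **Bronchoscopy does not decide the label.** A reader might infer that it does. A positive serum GM or sputum culture makes a CT-positive patient probable without BALF; on the step 3 figures, 46–71% of true IPA without BALF would still be probable. Hence the dependence is partial.
- **Analysis 1 is largely spared.** A reader might infer that both analyses are necessarily biased. Analysis 1 specificity is not, and its sensitivity shifts only if verification is related to the sputum marker. That is plausible, because sputum culture is in the reference standard, but it is not shown.
- **The fall to 0.69 is not the effect of missing BALF.** Correct: it is the effect of all missed IPA, and step 5 separates the two.
- **The two analyses already address possible IPA, and subset tables belong in an analysis plan.** The first half is true but does not help, since neither analysis separates unverified from BALF-negative patients. As to the second, the weakness is in the printed classification rule and in the printed use of possible IPA in analysis 2, not in a missing table.

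**Conclusion.** The point holds in limited form. The probable or possible label depends partly on whether BALF was obtained, and the protocol's passages on who has BALF do not agree. To the extent that BALF is missing, analysis 2 understates sputum specificity, PPV and AUC. If the marker tracks sputum culture, inflated sensitivity partly offsets the effect on AUC. Analysis 1 is affected only in sensitivity, and only under that condition.

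The size cannot be set from the document, which gives neither the share without BALF nor the sensitivity of BALF GM. The contrast of 29–54% with 3–16%, and the 0.02–0.09 of specificity, rest on assumed culture and BALF GM sensitivities, on independence, and on an assumed number and make-up of possible patients. They show direction and plausible order, and are not estimates for this trial.

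**What to change.** 1. Reconcile the Abstract and Discussion statements that BALF is collected with the either-specimen rule under Participants screening and recruitment, the entry criteria, and the remarks on feasibility. Say for whom BALF results are expected.
2. Under Statistical analysis, keep analysis 2 as it is and add a pre-specified sensitivity version. In it, possible IPA counts as non-IPA only if BALF was obtained and was negative, and possible IPA without BALF is shown as a separate row.
3. Repeat both analyses in the suspected patients who have BALF GM and BALF culture results, against the same no-IPA controls.
4. Tabulate BALF availability by IPA class.

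The cost is wording and extra analysis of data already collected. Intervals will be wider, and the subset in item 3 is limited to patients fit for bronchoscopy, so it should stand beside the planned analyses and not replace them. IPA missed despite BALF remains in every version.
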